### Primary outcome

The primary outcome is time to ulcer healing, which will be defined as ‘completed epithelial healing in the absence of scab (eschar) with no dressing required’. This will take the form of survival time data for analysis. Time to healing will be measured in days from the date of randomisation until the first date that healing is recorded. If healing occurs before the end of the study, the participant will be followed for a further 2 weeks to confirm healing, in accordance with the Food and Drug Administration (FDA) and European Wound Management Association (EWMA) guidelines [35]. A digital photograph of the area will be taken at this point to confirm healing. For patients who have not healed, time from date of randomisation until they exit the trial, withdraw, are lost to follow-up or die will be used in the survival analysis – whichever occurs first.

### Secondary outcomes

Secondary outcomes are:Ulcer size (area) measured in cm^2^ using image analysis by SigmaScan, Systat Software Inc, San Jose, CA, USA and/or wound tracingsRecurrence of reference ulcerAdverse events (AEs)Ulcer-related pain using a visual analogue scaleTreatment compliance (capsule counting and nurse assessment of compression concordance)Resource use: number of wound consultations and types of dressings used

### Statistical analysis

Analyses will be in accordance with the principles of intention-to-treat. Analysis will be conducted in Stata® (Stata Corporation, College Station, TX, USA) or similar statistical software. Statistical significance will be assessed at the 2-sided 5 % level unless otherwise stated. Ninety-five percent CIs will be provided as appropriate. Statistical analyses will be detailed in an analysis plan that will be independently reviewed and agreed before data are analysed.

#### Primary outcome analyses

Time to ulcer healing will be presented by trial arm using a Kaplan-Meier plot and a log-rank survival comparison will be made. The median time to healing will be presented overall and by trial arm with corresponding 95 % CIs. The primary analysis will investigate differences between trial arms in relation to time to ulcer healing using a Cox proportional hazards regression model. Adjustments will be made for log transformed area and duration of the reference ulcer. The model will be tested for inclusion of shared centre frailty effects.

#### Secondary outcome analyses

Ulcer area will be transformed and investigated on the natural log scale through mixed models to see whether there are differences by trial arm.

The proportion of patients who are found to have a recurrence within the study period will be reported by trial arm. Time from healing to recurrence will be investigated in a similar fashion to the primary outcome should numbers be sufficient to allow.

AEs will be reported overall and by trial arm in terms of number of patients with at least one event and total number of events. Serious and non-serious events will be presented separately and according to whether they are thought to be related, or unrelated, to treatment. Differences in total numbers of events by trial arm will be compared using negative binomial regression adjusting for size and duration of ulcer.

Mean and median pain scores will be presented by trial arm and differences in pain scores between the allocated groups will be investigated using linear regression adjusted for baseline pain score.

Compliance will be reported in terms of proportion of patients completing the course of treatment up to healing or planned trial exit and compared between arms using a Chi-squared test and 95 % CIs.

Resource use will be presented using summary statistics in relation to the number of wound consultations per week and change to compression therapy or primary wound dressings.

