### The need for AVURT – a randomised, placebo-controlled efficacy study

Whilst there have been two small trials to date that have investigated the use of aspirin in the treatment of VLUs, the quality of the evidence presented is low. Given the significant health burden represented by VLUs, and the challenges in treating the disease, there is a need to identify effective, inexpensive, safe and widely available treatments that patients may tolerate. The AVURT seeks to investigate the effect of aspirin on time to healing of VLUs, to examine safety issues in this cohort of patients and to inform on the feasibility of proceeding from a phase II trial to an efficacy and effectiveness (phase III) trial. If a simple, cheap and well-tolerated medication, such as aspirin, were to result in a reduction in time to healing, this would impact on patient management, resource use and the potential impact on the population is substantial, given that aspirin is widely available. Meta-analyses have demonstrated that low-dose aspirin increases the risk of major bleeding compared to placebo [32, 33]; however, the absolute increase is modest and there is no evidence that decreasing the dose will reduce the risks of side effects [34]. The study will also provide the opportunity to systematically review the safety profile of aspirin in this population of patients, as well as assess the generalisability of the medication by studying the number of patients with VLUs who are currently taking aspirin or other anti-platelet medications.

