### Randomisation and blinding

Participants will be randomised on a 1:1 basis to receive either aspirin (300 mg) or placebo, in addition to standard care. The Research Pharmacy responsible for dispensing all trial medication (St George’s Hospital) will receive a randomisation schedule generated in advance by the IMP manufacturer, Sharp Clinical Services UK Ltd. (Sharp Clinical Services, UK) Stratification will be by ulcer size (≤5 cm^2^ or > 5 cm^2^).

Randomisation will be performed by the Research Pharmacy upon receipt of a valid prescription for a participant. Researchers, treating staff, clinicians and participants will be blind to treatment allocation. A 24-hour code-breaking service will be provided by the Research Pharmacy in case of requirement for emergency unblinding and participants will receive a study-specific 24-hour emergency contact card.

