### Sample size calculation

This study aims to recruit 100 patients, which is sufficient to demonstrate whether there is evidence for efficacy of aspirin to treat VLUs, in line with previous similar trials [23, 24] and is also large enough to test the feasibility of study procedures such as recruitment.

The primary outcome is time to healing of the reference ulcer. Applying an assumed standard error for the hazard ratio (HR) of 0.105 following adjustment for log area and log duration of ulcer (as in VenUS IV) to the smaller sample size in this study implies that the standard error would be 0.22. A 95 % confidence interval (CI) for the log hazard ratio would thus be log(HR) ± 0.435. Hence, if the hazard ratio for this study were the same as that suggested by previous studies (around 1.5), the confidence interval would be (0.97, 2.31) which just includes 1.00. To further increase the power an IPD meta-analysis is proposed. As compliance and follow-up will be measured as part of the study there is no formal inflation for dropout.

An important secondary outcome is wound area. Assuming a standard deviation of 1.09 following log transformation as in (VenUS I) [15], 2 groups of 50 participants will render 80 % power to detect a difference of 0.62 on the natural log scale. This corresponds to a reduction of 46 % in ulcer area at follow-up. In the current study, there will be multiple measurements of wound area and so smaller differences should be detectable.

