### Safety reporting

Despite some apparent advantages of aspirin therapy in the treatment of VLUs, the risks associated with aspirin will carefully reported. Safety reporting during this trial is paramount and will be conducted in line with Healthy Technology Assessment (HTA) guidelines. Reportable safety events will include any of the following experienced by a participant during the trial: AE, adverse reaction, serious adverse event (SAE), serious adverse reaction (SAR), suspected unexpected SAR. All AEs will be recorded in the clinic notes, on the study CRF and reported to the sponsor via the sponsor AE log. SAEs and SARs will be notified to the sponsor immediately when the investigator becomes aware of the event (within 24 hours). The sponsor will inform the Medicines and Healthcare products Regulatory Agency (MHRA) and ethics committee, where appropriate. SAEs will be reported to the trial coordinator in the York Trials Unit via the sponsor and reviewed by the data monitoring committee.

All patients who develop unacceptable treatment toxicity which, in the investigator’s opinion, is attributable to the IMP or an SAE, will be withdrawn from the study treatment but follow-up will continue (where appropriate) to enable an intention-to-treat analysis. The side effects associated with aspirin are well-known to health professionals and no additional training will be required. These include, but are not limited to, gastrointestinal haemorrhage and gastrointestinal disturbance (including dyspepsia, ulceration).

In addition, AEs associated with leg ulceration or compression therapy will be recorded. Pregnancy and breastfeeding are exclusion criteria for the study; however, all patients of childbearing age will be advised to use barrier contraception during the duration of the study.

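### The one between-arm safety comparison the article specifies counts all adverse events together, so an excess of the bleeding and gastrointestinal harms it names for aspirin would be diluted

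*Protocol article*

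**What the plan says.** The abstract makes safety of aspirin in this population a secondary objective. The section on the need for the trial cites meta-analyses showing that "low-dose aspirin increases the risk of major bleeding compared to placebo", and adds that the absolute increase is modest. The section Safety reporting lists, among the known side effects of aspirin, "gastrointestinal haemorrhage and gastrointestinal disturbance (including dyspepsia, ulceration". It then adds that "AEs associated with leg ulceration or compression therapy will be recorded".

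Under Secondary outcome analyses, adverse events are to be reported overall and by arm, as participants with at least one event and as total events. Serious and non-serious events are shown separately and by judged relatedness to treatment. No test or interval is named for these tables. The inferential step is "Differences in total numbers of events by trial arm will be compared using negative binomial regression", adjusted for ulcer size and duration. No analysis by type of event is described, and no class of event is removed from the total.

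**The concern.** The article says which harms matter and then fixes a comparison that does not isolate them. A count of everything mixes possible aspirin reactions with events that belong to the ulcer, the bandaging and intercurrent illness. An excess confined to bleeding and gastrointestinal events is then averaged over all of these.

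A second route is specific to this trial. If aspirin hastens healing, which is the primary hypothesis, ulcer-related events may fall in the aspirin arm. That fall enters the same total and offsets any rise in bleeding. A pooled ratio near 1 could then reflect benefit and harm cancelling, not absence of harm. Both routes concern what is counted, so neither is cured by how time at risk is handled.

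At stake is whether this phase II trial, which is meant to inform a larger one, reports a usable estimate of the risk it identifies.

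**Working it through.** **Inputs from the article**
- Two-sided 5 % level: "Statistical significance will be assessed at the 2-sided 5 % level unless otherwise stated".
- Allocation: "Participants will be randomised on a 1:1 basis".
- Size: "This study aims to recruit 100 patients", so 50 per arm.
- Adverse event rates, overdispersion, or power for any safety comparison: none given.

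**The article's own power figure, as a check on the basis.** It states that "2 groups of 50 participants will render 80 % power to detect a difference of 0.62 on the natural log scale", with a standard deviation of 1.09. The standard error is 1.09 × √(2/50) = 0.218, so z = 0.62/0.218 = 2.84 and power = Φ(2.84 − 1.96) = 81 %. The stated 80 % is reproduced. It concerns wound area and says nothing about adverse events.

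**Direction of the dilution.** Let G be the mean number of bleeding/gastrointestinal events per participant on placebo, RR the true rate ratio for them, and B the mean number of other events, the same in both arms. Then

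pooled ratio = (B + G × RR) / (B + G).

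For any B > 0 this lies closer to 1 than RR. That step needs no assumed rates.

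**Size, under assumed rates.** Power uses the normal approximation for a negative binomial log rate ratio:

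SE² = (1/μ₀ + 1/μ₁ + 2k)/50,

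where μ₀ and μ₁ are mean events per participant on placebo and aspirin, and k is the overdispersion. Assume G = 0.3, RR = 2, B = 1.5, k = 0.5.

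| Count | Placebo | Aspirin | Ratio | Log ratio | SE | z | Power |
|---|---|---|---|---|---|---|---|
| All events | 1.8 | 2.1 | 1.17 | 0.154 | 0.202 | 0.77 | 12 % |
| Bleeding/gastrointestinal | 0.3 | 0.6 | 2.00 | 0.693 | 0.346 | 2.00 | 52 % |

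For the same rates with k from 0 to 1, power is 10–19 % pooled and 46–59 % separately. With k = 0.5, G from 0.2 to 0.4 and B from 1.0 to 2.0, it is 7–22 % pooled and 39–61 % separately.

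**Lower assumed rates.** With G = 0.2, RR = 2 and k from 0 to 1, the separate comparison has power 36–43 %. Pooling gives:

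| B | Pooled ratio | Power |
|---|---|---|
| 0.5 | 1.29 | 13–20 % |
| 1 | 1.17 | 9–14 % |
| 2 | 1.09 | 7–10 % |
| 4 | 1.05 | 6–8 % |

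With G = 0.1, even the separate comparison has power of only 22–24 %. Over a wider assumed grid (B 0.5–4, G 0.1–0.4, RR 2–3, k 0–1), pooled power was the lower in every case.

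**Cancellation.** If aspirin also cuts other events by 20 %, from 1.5 to 1.2, the pooled ratio in the main illustration is (1.2 + 0.6)/(1.5 + 0.3) = 1.00. With B = 2 and G = 0.2, a 10 % cut is enough: (1.8 + 0.4)/(2 + 0.2) = 1.00. In both cases a doubling of bleeding/gastrointestinal events leaves no trace in the pooled ratio.

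**The case against.** The strongest reply is that this belongs to the analysis plan. The article defers detail to a plan to be agreed before analysis, and events of special interest, coding and tables by type are commonly set out there. A reader might infer that the trial has no comparison by event type at all. The documents do not support that, because the analysis plan is not shown. What stands is that the article already fixes the outcome, model and covariates of a safety comparison, and that choice is poorly aimed at the harms it names.

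The planned tables also help. Staff and participants are blinded, so relatedness judgements should not favour an arm. Major bleeding would normally be classed as serious, and serious events go to the data monitoring committee. This is a real but partial safeguard: the tables carry no stated estimate or interval, are not by event type, and relatedness rests on judgement.

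Two further readings go too far. A reader might infer that ulcer and compression events dominate the count; the article says only that they are recorded and gives no frequency. A reader might also conclude that they should be left out of the safety comparison as not being harms of aspirin. The article does not establish that. Bleeding from the ulcer is ulcer-related and also a plausible aspirin effect, and comparing all events regardless of cause is legitimate in a blinded placebo-controlled trial.

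Finally, the separate comparison is itself weak. The 52 % depends on an assumed 15 extra events among 50 participants (0.3 × 50), and at lower rates power falls to between 22 % and 43 %. This stands, and it shapes the fix.

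**Conclusion.** The point holds as a matter of targeting. The one inferential safety comparison specified in the article pools the named aspirin harms with every other adverse event. The dilution towards 1 is certain in direction if aspirin does not affect other events. Complete cancellation is possible if it reduces them, but nothing in the article shows that this would happen.

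The size is not derivable from the document. Under the assumed rates, a true doubling shows as a pooled ratio of about 1.05 to 1.29, with power mostly below about one in five. Power for the named harms alone is roughly 36–61 % at 0.2 to 0.4 events per participant, and lower for rarer events. The gain is therefore an undiluted estimate with an honest interval, not a reliable test. The primary analysis is unaffected. The change is worth making because safety is a stated objective and the remedy is cheap.

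**What to change.** Under Secondary outcome analyses:

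- Pre-specify two groups of events of special interest: bleeding events, including bleeding from the ulcer, and gastrointestinal events. State to which group a gastrointestinal haemorrhage is assigned, or that it counts in both.
- For each group, report by arm the number of participants with at least one event and the number of events, with a between-arm estimate and 95 % CI. Say that these are estimates and not confirmatory tests, since power is low at 50 per arm.
- Tabulate ulcer- and compression-related events separately for description, and keep them in the all-event comparison.
- Retain the negative binomial comparison of all events and the tables by seriousness and relatedness.

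If the analysis plan already does this, aligning the article's wording with it is enough.

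The cost is coding, by type, events already on the case report form and the adverse event log, best done while blinded, plus two extra estimates that will be imprecise. No visits, participants or clinical procedures change.

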### Treatment period and follow-up

After consent, participants will be screened to ensure eligibility. Prior to randomisation, baseline demographic details will be collected and a clinical assessment of the patient and wound performed. Following randomisation, participants will continue in the normal care pathway of weekly or 2-weekly clinical assessments at community ulcer clinics, hospital outpatient clinics or home visits and will not be required to attend any further visits for research purposes. All randomised participants will receive aspirin or placebo for 24 weeks and will be followed-up for 25 weeks following randomisation. If the reference ulcer is confirmed as healed during the follow-up period, then a photograph will be taken and the participant will continue to take the IMP or placebo for 2 further weeks. They will then be re-assessed (as per FDA and EWMA guidelines on wound healing) [35]. If the ulcer is confirmed as healed at this reassessment visit, then the date of ulcer healing will be recorded as the date that the ulcer was first assessed as healed. The participant will then be advised to stop taking the IMP or placebo. If a new ulcer occurs on the reference leg before the end of the study, then participants will be asked to inform the study team.

If the ulcer is assessed as ‘not healed’, then the participant will continue in the trial until the minimum period of follow-up (25 weeks) has elapsed providing confirmed healing does not occur before the end of the follow-up period. Both of these time-points (first healing judgement and confirmation of ulcer healing) will be recorded.

Participants will also be asked to provide a pain score using a visual analogue scale at baseline and 4–6 weeks after first dose of IMP. Weekly (or 2-weekly, if that is the participant’s usual interval of care) assessments will include: healing outcomes, treatment concordance with IMP and compression bandaging, AEs or side effects, change to concomitant medication, resource use (number of visits, types of dressings used and level of compression). Digital photographs, or leg ulcer tracings, will also be taken by the treating or research nurse.

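### Adverse-event totals are compared with no term for time at risk, although time on drug, and by one reading observation too, ends soon after healing

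*Protocol article*

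**What the plan says.** All references are to the protocol article.

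- **Secondary outcome analyses, model:** "Differences in total numbers of events by trial arm will be compared using negative binomial regression adjusting for size and duration of ulcer". The response, the model family and the adjustment variables are named. An offset, exposure term or rate is not.
- **Secondary outcome analyses, summaries:** "AEs will be reported overall and by trial arm in terms of number of patients with at least one event and total number of events". Neither summary uses time. Resource use in the same section is put on a time scale, as "summary statistics in relation to the number of wound consultations per week".
- **Treatment period and follow-up, healed participants:** after the first healing judgement, "the participant will continue to take the IMP or placebo for 2 further weeks". If healing is confirmed at reassessment, "The participant will then be advised to stop taking the IMP or placebo".
- **Primary outcome:** "If healing occurs before the end of the study, the participant will be followed for a further 2 weeks to confirm healing".
- **Treatment period and follow-up, participants not healed:** "the participant will continue in the trial until the minimum period of follow-up (25 weeks) has elapsed", on condition that healing is not confirmed sooner.
- **Treatment period and follow-up, everyone:** the same section also gives all randomised participants 24 weeks of treatment and 25 weeks of follow-up. The Abstract gives a maximum of 27 weeks.
- **AE collection:** AEs are recorded at the usual weekly or 2-weekly ulcer visits, and no additional visits are made for research.

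**The concern.** A negative binomial model without an offset compares mean counts per participant. Those means compare AE rates only if the arms are at risk for equally long. Here the end of treatment, and possibly the end of observation, is triggered by healing, which is the primary outcome. An arm that heals faster has fewer days in which events can occur or be recorded. Adjusting for baseline ulcer size and duration does not correct this, because randomisation balances those variables while the difference in time at risk arises afterwards.

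Safety of aspirin is a stated objective, and the article itself cites an increased risk of major bleeding. The count comparison would understate aspirin's AE rate in the very case where the efficacy result would favour going on to phase III.

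**Working it through.** **The plan's own figure.** None is given for the AE comparison. The hazard ratio used below is the one in the sample size section. Its interval reproduces: exp(ln 1.5 ± 1.96 × 0.22) = (0.97, 2.31).

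**Inputs from the article**
- Healing hazard ratio 1.5 (Sample size calculation).
- Median healing time 99 days (Background, from a cited study of 2-layer compression), used here for the control arm.
- 14 days from first healing to confirmation.
- End of follow-up at 25 weeks = 175 days.

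**Assumptions not in the article:** exponential healing times, and an AE rate that is constant over time.

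**Reading A: observation ends when healing is confirmed.** Time at risk is min(T + 14, 175), where T is the healing time. Its mean is

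14 + (1 − exp(−λ × 161)) / λ, with λ = (ln 2 / 99) × HR.

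- Placebo: λ = 0.00700, mean = 14 + 96.6 = 110.6 days.
- Aspirin: λ = 0.01050, mean = 14 + 77.7 = 91.7 days.
- Ratio = 91.7 / 110.6 = 0.83.

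The expected count ratio is the true rate ratio times 0.829:

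| True AE rate ratio | Count ratio without offset |
|---|---|
| 1.00 | 0.83 |
| 1.25 | 1.04 |
| 1.50 | 1.24 |

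A true rate ratio of 110.6 / 91.7 = 1.21 would look like no difference.

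**Sensitivity of the 0.83**
- Control median 60 to 250 days, at hazard ratio 1.5: 0.78 to 0.91.
- Hazard ratio 1.25: 0.91. Hazard ratio 2.0: 0.71. Hazard ratio 1.0: 1.00.
- Cap of 168 days: 0.835. Cap of 189 days (27 weeks): 0.819.

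**Simulation under reading A.** 1,000 trials per scenario, 50 per arm, without the ulcer covariates, with an assumed 0.02 AEs per day and gamma frailty variance of 1:

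| True rate ratio | Estimate, no offset | Estimate, log(time) offset |
|---|---|---|
| 1.0 | 0.82 | 0.99 |
| 1.25 | 1.03 | 1.24 |
| 1.5 | 1.22 | 1.49 |

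At equal rates, the model without an offset showed significantly fewer AEs on aspirin in 12.4 % of trials (nominal 2.5 %), against 2.6 % with the offset. At a true ratio of 1.5, it showed significant harm in 12 % of trials, against 37 % with the offset. These percentages depend on the assumed rate and frailty. The expected count ratios in the first table do not.

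**Reading B: AEs are collected to week 25 in everyone.** Observed time is then about 175 days in both arms, so an offset for observed time is nearly constant and changes almost nothing. Only time on drug differs. Suppose aspirin raises the AE rate 1.5-fold, but only while it is taken. The expected count ratio is

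(1.5 × 91.7 + 1.0 × (175 − 91.7)) / 175 = (137.6 + 83.3) / 175 = 1.26.

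Capping drug time at 24 weeks (mean 90.3 days) also gives 1.26. Under this reading, the on-drug ratio is recovered only by using on-treatment events and on-treatment time.

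**The case against.** **An offset is detail for the analysis plan.** The article promises a separate plan, which is not shown and may include an offset. Naming two covariates does not rule one out. This lowers the severity but does not remove the point: the article fixes response, model and adjustment set for a stated comparison, and a plan that follows it literally carries the problem forward.

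**The end of assessment is an inference.** A reader might conclude that AE assessment certainly stops at healing. The documents do not support that. Drug stops at confirmation, about 2 weeks after healing is first seen. That observation stops then is implied by the Primary outcome section and by the condition attached to participants not healed. Against it stand the statement that all are followed for 25 weeks, recurrence as an outcome, and safety reporting that covers events during the trial with no cut-off at healing. This objection stands in full: the 0.83 belongs to reading A only.

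**Counts are a legitimate target.** Under treatment until healing, total AEs per randomised participant measure the burden of the strategy. Fewer ulcer- or compression-related events because the ulcer healed is a real benefit. An offset brings in a post-randomisation quantity and answers a different question. This also stands, so the counts should be kept and the rate added beside them.

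**Safety does not rest on this model alone.** Participants with at least one event are reported, events are split by seriousness and relatedness, and the data monitoring committee reviews serious events. That is true, but the planned AE summaries are not per unit of time either.

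**Conclusion.** The point holds with limits. As written, the only formal AE comparison uses totals with no time at risk, while time on drug depends on healing. At the protocol's own hazard ratio of 1.5 and a 99-day control median, the AE rate ratio is understated by about 17 % if observation ends at confirmed healing (9 % to 22 % for control medians of 250 down to 60 days). If everyone is observed to week 25, a 1.5-fold excess confined to time on drug appears as about 1.26. Both results assume exponential healing and constant AE rates.

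A reader might infer that the analysis will make aspirin look safer than it is. The documents do not support that as a general statement. The effect needs aspirin to speed healing and vanishes on average if it does not; the hazard ratio of 1.5 comes from trials that the article itself calls low quality; and the counts remain valid as a measure of burden. Severity is moderate.

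**What to change.** 1. Keep the raw counts, labelled as AE burden per randomised participant.
2. Add a negative binomial comparison with log(person-time at risk) as offset, and report AEs and serious AEs per person-time by arm. Do this twice: with all events over observed time, and with on-treatment events over on-treatment time (start to stop of study drug plus a stated window). An observed-time offset alone is not enough, because it does nothing if everyone is observed to week 25.
3. State the AE collection window for participants whose ulcer has healed.
4. Reconcile the follow-up and treatment-duration statements in the Abstract, Primary outcome, and Treatment period and follow-up sections.

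The cost is small: a few lines in the analysis plan. The article already has both healing time-points recorded and drug concordance assessed at each visit; whether the case report form captures the actual stop date and the last AE assessment should be checked. The downside is a second AE estimate that conditions on exposure after randomisation, so it must be labelled as a rate and not as a burden.

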Over a decade later, a Spanish group conducted a small randomised pilot trial (*n* = 51 patients) of aspirin and compression, demonstrating that aspirin reduced the average time to healing but did not influence the rate of healing and had no effect on the rate of ulcer recurrence. In addition, after multivariate analysis was performed, aspirin was not demonstrated to be an independent predictor of healing [24] with only initial ulcer size at study entry remaining independently associated with rate of healing. Moreover, no information was presented regarding the placebo and there is uncertainty around the effect estimates. The quality of evidence that aspirin hastens healing of VLUs is, therefore, low and needs addressing through more robust studies.

In addition to the Aspirin for Venous Ulcers: Randomised Trial (AVURT), there are two ongoing randomised trials investigating the use of aspirin in VLU. ASPiVLU (ASPirin in Venous Leg Ulcer healing, ACTRN12614000293662) will investigate the use of 300 mg aspirin, in addition to standard 3-layer compression therapy, with the primary endpoint as the time to complete ulcer healing at or before 12 weeks from randomisation. Aspirin4VLU (Low Dose Aspirin for Venous Leg Ulceration, NCT02158806) will investigate 150 mg aspirin, in addition to routine care, on time to complete healing of the reference ulcer. In addition to the trials reporting individually, data from AVURT, ASPiVLU and Aspirin4VLU will be combined in order to carry out an individual patient data (IPD) meta-analysis. Any other relevant trials such as the two earlier trials will also be considered for inclusion.

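### The ulcer-area mixed model names no baseline area or duration, although the primary and adverse-event models adjust for both; the pain regression, a minor point, omits only the size stratifier

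*Protocol article*

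**What the plan says.** All references are to the protocol article.

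- **Ulcer area (Secondary outcome analyses).** Log area is to be "investigated on the natural log scale through mixed models to see whether there are differences by trial arm". No baseline area, size stratum or duration is named.
- **Pain (same section).** The text states that "differences in pain scores between the allocated groups will be investigated using linear regression adjusted for baseline pain score". Ulcer size is not in that adjustment set.
- **Other models.** Primary outcome analyses adjusts the Cox model for log area and duration. Secondary outcome analyses adjusts the negative binomial model for adverse events for size and duration.
- **Randomisation and blinding.** "Stratification will be by ulcer size", with one cut at 5 cm².
- **Aspirin (background).** An earlier pilot trial of 51 patients is reported "with only initial ulcer size at study entry remaining independently associated with rate of healing".
- **Sample size calculation.** Wound area is described as an important secondary outcome. With an SD of 1.09 on the log scale, "2 groups of 50 participants will render 80 % power to detect a difference of 0.62 on the natural log scale", and "This corresponds to a reduction of 46 % in ulcer area at follow-up". The section adds that repeated measurements should allow smaller differences to be detected. It does not mention baseline adjustment for this outcome.
- **Statistical analysis.** A separate analysis plan is to give the detail. It is not at hand.

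**The concern.** The article names adjustment variables for the Cox, adverse-event and pain models. The area model is the one regression given a sentence of its own that names none. It is also the model in which baseline size matters most, because baseline size is there the outcome's own starting value.

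Read literally, a comparison by arm alone has two consequences:

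- Between-patient variation in starting area stays in the error term. The standard error is then wider than it need be, and conservative for a design stratified on size.
- Chance imbalance within strata goes uncorrected. Eligibility sets a lower limit of more than 1 cm² and no upper limit, so the upper stratum is open-ended. With 50 patients per arm, some imbalance in starting area within it is plausible.

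The stake is precision on a secondary outcome that the article itself powers. For pain the issue is only consistency with the stratified randomisation.

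**Working it through.** **Inputs from the article.** 50 per arm (1:1); SD of log area 1.09; difference 0.62; power 80 %; two-sided 5 % ("Statistical significance will be assessed at the 2-sided 5 % level unless otherwise stated").

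**Inputs assumed, because the article gives none.** The correlation ρ between baseline and follow-up log area, taken as 0.3 to 0.8. For pain, the partial R² of ulcer size beyond baseline pain, taken as 0.01 to 0.10.

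**1. The stated power reproduces.**

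- SE = 1.09 × √(2/50) = 0.218.
- 0.62 / 0.218 = 2.844, so power = Φ(2.844 − 1.960) = 0.812. A t-based calculation with 98 degrees of freedom gives 0.804.
- Detectable difference by the normal formula: 0.218 × (1.960 + 0.842) = 0.611, close to the stated 0.62.
- 1 − exp(−0.62) = 46.2 %, as stated.

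**2. Area, if 1.09 is an unadjusted SD.** At a single follow-up time, adjustment for log baseline area multiplies the SD by √(1 − ρ²).

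| ρ (assumed) | SE ratio | Detectable difference at 80 % power | Area reduction | Power at 0.62 |
|---|---|---|---|---|
| 0 | 1.000 | 0.611 | 46 % | 0.812 |
| 0.3 | 0.954 | 0.583 | 44 % | 0.846 |
| 0.5 | 0.866 | 0.529 | 41 % | 0.907 |
| 0.6 | 0.800 | 0.489 | 39 % | 0.945 |
| 0.7 | 0.714 | 0.436 | 35 % | 0.978 |
| 0.8 | 0.600 | 0.366 | 31 % | 0.997 |

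**3. Area, if 1.09 is already baseline-adjusted.** The gain in step 2 is then already inside the stated 80 %. A single-time comparison without the covariate would face an SD of 1.09 / √(1 − ρ²):

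- ρ = 0.3: SD 1.143, SE 0.229, power at 0.62 = Φ(2.713 − 1.960) = 0.77.
- ρ = 0.5: SD 1.259, SE 0.252, power = Φ(2.463 − 1.960) = 0.69.
- ρ = 0.8: SD 1.817, SE 0.363, power = Φ(1.706 − 1.960) = 0.40.

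Either way, the model sentence needs the covariate.

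**4. Do repeated measurements make it unnecessary?** As an illustration, take six follow-up measurements with a common correlation ρ among them and with baseline. Averaging multiplies the variance by (1 + 5ρ)/6; adjusting for baseline as well subtracts ρ². Each detectable difference is 0.611 times the square root of the variance factor.

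| ρ (assumed) | Factor, averaging only | Difference | Factor, with baseline | Difference |
|---|---|---|---|---|
| 0.5 | 0.583 | 0.47 | 0.583 − 0.25 = 0.333 | 0.35 |
| 0.8 | 0.833 | 0.56 | 0.833 − 0.64 = 0.193 | 0.27 |

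Averaging helps least when correlation is high, which is where the baseline helps most.

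**5. Pain.** Adding ulcer size to a model that holds baseline pain multiplies the SE by √(1 − partial R²).

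- 0.01: ratio 0.995; a comparison at 80 % power rises to 80.4 %.
- 0.05: ratio 0.975; 82.0 %.
- 0.10: ratio 0.949; 84.0 %.

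Allowing for the extra degree of freedom (a further factor √(97/96)), the gain at 0.01 disappears (ratio 1.000), and at 0.10 the ratio is 0.954.

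**The case against.** The strongest reply is that the area sentence gives a model family and a purpose, and no fixed effects at all. It does not call the model unadjusted. A mixed model can carry baseline area as a covariate or as the first repeated measure, and the article defers detail to an analysis plan that is not shown. This stands in part: a reader might infer that baseline area is excluded, and the text does not say so. What remains is that the article chose to name adjustment variables for the neighbouring models and not for this one, so the current wording does not commit the trial to the adjustment.

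The size of the gain is also conditional. ρ is assumed, the source of the 1.09 cannot be seen, and step 2 treats one time point instead of the planned repeated measures. All of that stands. The article describes the hazard-ratio standard error as adjusted for log area and log duration but the 1.09 only as log-transformed. That leans towards an unadjusted SD without settling it.

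Three stronger readings should be set aside:

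- **Both secondary models lack the outcome's baseline value.** The pain sentence itself shows that baseline pain is included.
- **The comparison would be invalid.** In a linear model, leaving out a stratification factor costs precision and makes standard errors conservative. It does not inflate the type I error.
- **The power statement is wrong.** It reproduces.

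Finally, the finding on initial size comes from a single small pilot whose evidence the article itself calls low quality, and it concerns healing, not pain. The case for the area covariate does not depend on it.

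**Conclusion.** The point holds for ulcer area as under-specification with a real but unquantified cost in precision. With 1.09 unadjusted and ρ between 0.3 and 0.8, the detectable difference at one time point falls from about 0.62 (46 % reduction) to between 0.58 and 0.37 (44 % to 31 %) at the same sample size. With 1.09 already adjusted, the stated 80 % depends on a covariate that the model sentence does not name. For pain, the point is minor: only the size stratifier is absent, and the likely gain is about 0.5 % to 5 % off the standard error under the assumed partial R², before the small cost in degrees of freedom. The primary analysis is unaffected, since it already adjusts for log area and duration.

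**What to change.** In the analysis plan, state that the area mixed model includes log baseline area and log duration of the reference ulcer, in line with the primary model. Also state whether the 1.09 is an unadjusted or a baseline-adjusted SD, so that the power statement and the model agree. For consistency with the randomisation, add log area or the ≤5 / >5 cm² stratum to the pain regression alongside baseline pain.

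The cost is a few lines of wording before data are analysed. The wound is assessed before randomisation and the same covariates already enter the Cox model, so no new data and no change in sample size are needed. Naming the covariates in advance also removes any later choice about them.
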